##### Mammography Satisfaction Variation

We will use descriptive statistics to explore the extent to which the mammography experiences and mammography satisfaction of American Indian/Alaskan Native women vary. Frequencies and percentages will be used to summarize categorical demographic information of the participants surveyed. The primary outcome will be the global satisfaction score on the AIMS with secondary outcomes being the derived AIMS subscales. AIMS subscales will be derived from barriers cited by focus group participants and confirmed through factor analytic procedures conducted during the AIMS pilot test. Projected subscales will include service accessibility, results reporting procedures, staff interpersonal skills, perceived technical competence of staff, and global satisfaction. To model the global AIMS scores on individuals adjusting for individual factors (age, race/ethnicity, etc.), linear regression models will be developed. Similar models will be developed for AIMS subscale scores.

Using global patient satisfaction as the primary outcome variable, we also then conduct comparison of AIMS survey characteristics between women who sought services within and outside of the Indian Health Service system. This will be done by averaging the global AIMS scores for participants with an Indian Health Service-sponsored mammogram and those with a non-Indian Health Service-sponsored mammogram. Similar averaging will be done for each AIMS subscale to obtain global AIMS subscale scores.

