Two validated mammography patient satisfaction surveys have been developed. The first measure, developed by Loeken et al, is a 27-item instrument that emphasizes patient discomfort during mammography. This instrument includes eight subscales: physical discomfort, psychological discomfort (awkwardness, embarrassment), staff interpersonal skills, information transfer (explanation of procedure, comfort with asking questions), physical surroundings (ambience of waiting and examination rooms), future general satisfaction (advising others to have a mammogram), present general satisfaction (ensuring comfort), and staff technical skills [68,69]. The reliability, validity, and discriminatory power of this instrument have been examined with satisfactory results. All studies were conducted in Norway. Loeken and her colleagues subsequently used their instrument to compare patient satisfaction levels among six mammography facilities in Norway [70]. This study found considerable variation among facilities with respect to patient-reported pain, staff punctuality, information provided, and physical surroundings. To date this is one of the largest comparisons of patient satisfaction among mammography facilities.

The second measure, developed by Cockburn et al, is a 26-item instrument with six subscales: 1) convenience and accessibility, 2) staffs' interpersonal skills, 3) information transfer, 4) physical surroundings, 5) perceived technical competence of staff, and 6) general satisfaction. Cockburn's assessment of convenience and accessibility included waiting time, convenience of facility location, hours of operation. Questions on staff interpersonal skills included feeling hurried and politeness of staff. Information transfer questions covered explanation of the mammography procedure and an assessment of comfort with asking questions. Physical surroundings involved assessment of privacy and waiting room ambience. Questions on perceived technical competence were focused on mammography technologists. A general satisfaction subscale tapped into a woman's intent to return for screening. The reliability and concurrent and discriminant validity of this instrument have been examined. All studies on psychometric properties of this instrument were conducted in Australia.

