#### AIMS Pilot Test

We will conduct mock tests of the AIMS Internet instrument and analyze the questions for logistical problems such as skip patterns, range errors, and response issues. Once all logistical issues are resolved, we will pilot the AIMS Internet survey with a sample of 50 American Indian/Alaskan Native women. The pilot testing procedure described below will allow us to administer the AIMS to a sample of women to determine if the questions are presented in a clear and understandable manner, assess the face validity of the questions, and evaluate the survey administration procedure. The pilot test will help guide the final refinement of the AIMS.

After completing the AIMS web survey, additional questions will be tagged on the end of the assessment that inquire about: 1) whether participants felt the survey questions clearly assessed the important aspects of mammography services, mammography satisfaction and dissatisfaction, and barriers to mammography utilization, 2) whether participants felt comfortable responding to all of the questions, 3) perceptions regarding the clarity and completeness of the information included in the AIMS survey, 4) the personal relevancy of the survey topics, and 5) the readability/presentation of the AIMS survey. Survey items will be revised based on feedback and re-piloted with additional participants until an acceptable AIMS survey has been developed.

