### Study 3: Assessment of Variation in American Indian Mammography Satisfaction

#### Full AIMS Implementation Procedure

##### AIMS Recruitment

As with the focus group and AIMS pilot testing portions of this study, AIMS survey participants will be recruited at the Haskell Health Center through referral from clinic personnel and through posters in the waiting area. We will also recruit at 4-5 AI/AN community events held each year (one event in each of the four Kansas-based reservation cities (e.g., Horton, White Cloud, Mayetta, and Reserve, KS). These community events will include health fairs and Pow Wows. This multi-method plan of recruitment will allow us better access to participants who do not use IHS facilities for mammograms. In advance of events, we will post flyers and posters at various community locations in the four primary Kansas Indian Reservation sites and at the Haskell Health Center. We will also post informational flyers at other local AI/AN venues including the Heart of America Indian Center and the offices of the American Indian Council. We will make two Internet-ready laptop computers available at each community event so that interested participants readily may complete the AIMS survey. Postcards with the Healthy Living American Indian Women website address will be provided to those women who express interest but who prefer to complete the assessment in the comforts of another environment (e.g., their home or local library). An additional paper and pencil version of the AIMS survey will be available on site at community recruitment events for those individuals preferring a non-electronic information submission approach.

The Principle Investigator and Project Manager will maintain close contact with key community member stakeholders involved in the proposed recruitment venues and will conduct ongoing assessments of the feasibility of the procedure used to identify women for the AIMS survey. Appropriate adjustments in the recruitment protocol will be made to meet survey accrual needs.

Eight to 10 subjects per AIMS survey item will be used during this study (for example, if 25 items are included in the instrument, 200-250 patients will be used). We will mail postcard reminders and telephone persons who were recruited and expressed an interest in participating in the AIMS on their own time but who fail to engage with the survey to maximize recruitment efficiency and survey completion.

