##### Reliability

The test-retest reliability, or reproduciblity, of a survey instrument refers to its ability to consistently measure all domains of diseases-specific functional status over time in a stable cohort of patients [98-100]. The more reliable, or reproducible, a measure is, the smaller the required sample size for meaningful applications of the questionnaire. Exploratory factor analysis will be used to measure reliability (using Cronbach's coefficient alpha [101]). The existing scales from the Cockburn and PAMS instruments as well as constructs derived from the focus groups will be used as the theoretical basis for naming factors revealed by this factor analysis.

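### The AIMS subscales, which are the secondary outcomes, are to be confirmed by factor analysis in a 50-woman pilot that is too small for it, although the roughly 300 women of Study 3 could carry the analysis

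*Protocol article*

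**What the plan says.** Four parts of the protocol article bear on where the subscale structure is settled.

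- **Mammography Satisfaction Variation (Study 3).** The global AIMS score is the primary outcome, "with secondary outcomes being the derived AIMS subscales". The subscales come from barriers named in the focus groups and are then "confirmed through factor analytic procedures conducted during the AIMS pilot test". Five subscales are projected.
- **AIMS Pilot Test (Study 2).** "we will pilot the AIMS Internet survey with a sample of 50 American Indian/Alaskan Native women". The stated purposes are clarity, face validity and the administration procedure; factor analysis is not among them. The section adds: "Survey items will be revised based on feedback and re-piloted with additional participants until an acceptable AIMS survey has been developed".
- **AIMS Recruitment (Study 3).** "Eight to 10 subjects per AIMS survey item will be used during this study", with the example that "if 25 items are included in the instrument, 200-250 patients will be used". The final item count is not fixed. One of the two source instruments, the Australian one, "is a 26-item instrument with six subscales", and the AIMS is to modify and supplement it.
- **Reliability (Study 3 Data Analysis).** An exploratory factor analysis is planned, in which existing scales and "constructs derived from the focus groups will be used as the theoretical basis for naming factors revealed by this factor analysis". The section does not mention the pilot confirmation.

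The section on developing the AIMS survey defines each subscale score as the sum of its item scores, and the global score as the sum of the subscale scores.

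**The concern.** A factor analysis that is said to confirm a multi-subscale structure needs enough respondents to estimate the item correlations with reasonable precision. Fifty women is a sensible number for testing wording and skip patterns, but a small one for confirming five subscales.

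Two things are at stake. If the subscales are fixed on the pilot, the secondary outcomes in Study 3 may group items partly by chance, and the domain-wise alphas and the subscale regression for discriminant validity would inherit that grouping. Also, Aim 2 promises a psychometrically validated instrument, and a structure called confirmed on 50 women is weak support for that. The Reliability section plans a second factor analysis on the larger sample but does not say whether it can revise the pilot structure, so no rule governs the case where the two disagree.

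**Working it through.** **1. The protocol's own figure.** Inputs: 8 to 10 subjects per item and 25 items (AIMS Recruitment). 8 × 25 = 200 and 10 × 25 = 250. The stated 200 to 250 is reproduced.

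**2. The pilot on the same yardstick.** Women per item = sample size / items.

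- 25 items: 50 / 25 = 2.0
- 26 items (the Australian source instrument alone): 50 / 26 = 1.9
- Assumed range of 20 to 40 items: 50 / 20 = 2.5 down to 50 / 40 = 1.25
- Largest instrument for which 50 women suffice: 50 / 10 = 5 items to 50 / 8 = 6.25 items

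**3. The Study 3 sample.** The Sample Size Justification plans 300 women. 300 / 25 = 12.0 per item. Eight per item still holds at 37 items (300 / 37 = 8.1) but not at 40 (300 / 40 = 7.5).

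**4. What 50 women can recover.** The protocol gives no loadings or factor correlations, so these are assumptions: 25 items, five factors with five items each, and equal loadings. Items were assigned to their largest loading with the number of factors given. The number of factors was judged separately by parallel analysis.

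*Run A:* principal-axis factoring with varimax, factor correlation 0.3, parallel analysis against mean random eigenvalues, 400 samples per cell.

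| Loading | All 25 items right, N=50 | Five factors found, N=50 | Mean items misplaced, N=50 |
|---|---|---|---|
| 0.5 | 0% | 16% | 7.9 |
| 0.6 | 16% | 21% | 2.8 |
| 0.7 | 82% | 47% | 0.25 |

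At N=300 both criteria succeeded in 98 to 100% of samples.

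*Run B:* principal-axis factoring with promax, parallel analysis against the stricter 95th percentile, 150 samples per cell.

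| Loading | Factor correlation | All items right, N=50 | Five factors, N=50 | All items right, N=300 | Five factors, N=300 |
|---|---|---|---|---|---|
| 0.5 | 0.3 | 0% | 2% | 100% | 93% |
| 0.5 | 0.5 | 0% | 0% | 73% | 9% |
| 0.6 | 0.3 | 16% | 3% | 100% | 100% |
| 0.6 | 0.5 | 1% | 0% | 100% | 63% |
| 0.7 | 0.3 | 77% | 25% | 100% | 100% |
| 0.7 | 0.5 | 33% | 1% | 100% | 99% |

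The runs agree closely on item assignment at correlation 0.3. They differ on the factor count because run B uses the stricter threshold. With 150 samples, the Monte Carlo standard error of a percentage is at most √(0.25 / 150) = 4 points.

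**5. If confirmation means a confirmatory model.** With five correlated factors and 25 items, each loading on one factor, the free parameters are 25 loadings + 25 residual variances + (5 × 4) / 2 = 10 factor correlations = 60. That exceeds the 50 women in the pilot. In 300 women it is 300 / 60 = 5 women per parameter.

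**6. Effect on the primary outcome.** Global score = sum over subscales of (sum of items in each subscale) = sum of all items. Moving an item from one subscale to another leaves this total unchanged.

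**The case against.** The strongest case against is that little hangs on the pilot analysis. The subscales are derived from existing instruments and focus groups, so the pilot checks a given grouping and does not search for one. Blind assignment to the largest loading, as simulated, is the harder task. The assumed loadings also matter: at 0.7 with weakly correlated factors, 98% of items are placed correctly even at N=50 (run B). Study 3 has its own factor analysis, domain-wise alphas and subscale regression, and nothing says that its subscales must be scored on the pilot structure whatever those show. The lock described under Survey Form Development concerns format and editing of the form, not scoring.

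Much of this stands and limits the point. It does not remove it: confirmation is tied to the pilot in so many words, a confirmatory model would have more parameters than women, and nothing gives the Study 3 analysis authority over the subscales.

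A reader might also infer several stronger things that the documents do not support:

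- *That the primary outcome is compromised.* Regrouping does not alter the global score. Only dropping items could, and no section drops items on the pilot factor analysis. Items are dropped on expert content ratings and revised on participant feedback.
- *That the pilot breaches a stated rule.* The 8 to 10 per item is written for the Study 3 survey, and 25 items is an example. It is a yardstick here.
- *That the 50 women answered different versions.* Re-piloting uses additional participants, so the 50 plausibly see one version. Extra rounds may add women, but no number is given, and revised items would limit pooling.
- *That the Reliability and Mammography Satisfaction Variation sections contradict each other.* Both analyses can be done. What is missing is how they relate.
- *That 300 women guarantee recovery.* They do not when loadings are low and factors are more strongly correlated.

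**Conclusion.** The point holds as one that should be fixed, not as a fatal flaw. Fifty women, about 2 per item at the illustrative 25 items, cannot reliably confirm a five-subscale structure. With factors correlated 0.3, the complete grouping is right in 0 to 82% of samples across loadings of 0.5 to 0.7, and five factors are found in at most 47%. At correlation 0.5 these ranges fall to 0 to 33% and 0 to 1%. Study 3's 300 women do far better in every setting tried; the weakest result there is 73% for the complete grouping and 9% for the factor count, at loading 0.5 and correlation 0.5.

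These percentages rest on assumed loadings, correlations and item count, and on data-driven assignment, so they show direction and rough size only. The per-item ratios depend only on the item count, and any instrument of more than six items falls below 8 per item in the pilot. The consequence is confined to the secondary outcomes and the validation claim of Aim 2.

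**What to change.** 1. In Mammography Satisfaction Variation, delete the factor-analytic confirmation in the pilot, or label it preliminary and without effect on scoring. Keep the pilot to the purposes listed under AIMS Pilot Test.
2. Before Study 3, prespecify the subscales and their items from the Australian instrument, PAMS and the focus-group constructs.
3. Test that structure by confirmatory factor analysis in the Study 3 sample of about 300. Prespecifying the number of factors avoids relying on a data-driven count, which is the weakest element even at 300.
4. State in both Reliability and Mammography Satisfaction Variation that this analysis settles the subscales, and that exploratory analysis is used only if the prespecified structure fails criteria stated in advance.
5. Fix the scoring and fallback rule before the IHS versus non-IHS comparison is run, and apply it without reference to IHS group.

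The cost is wording, with no additional participants. The downside is that subscale scoring becomes final only after the Study 3 data are in, and an exploratory fallback on the same women makes scoring data-dependent; step 5 is there to contain that. If the final instrument exceeds 37 items, 300 women would no longer give 8 per item, and the sample would need another look.

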### Access to Mammography

Access issues that may be classified as barriers to mammography include limited hours of operation, acceptance of self-referrals, ease of making an appointment, waiting room time, the use of reminder postcards or telephone calls, and location/type of facility. For the AI/AN population, this may also entail the pervasive unavailability of Indian Health Service practitioners and facilities. For example, all enrolled members of federally-recognized tribes are eligible for free health services at Indian Health Service (IHS) facilities and most AI/AN receive at least some of their care at IHS facilities. The IHS has 12 area offices overseeing 550 healthcare facilities across the US. The IHS does not have funding to place mammography machines in all clinics or to transport women to clinics that have them [57]. As such, many women go outside the IHS for screening.

A local IHS facility, Haskell Health Center (HHC) in Lawrence, KS (approximately 40 miles from the Kansas City Metropolitan area), serves approximately 8500 urban and rural (on- and off-reservation) AI/AN, and is administered by the Oklahoma City area office and staffed by a variety of medical professionals including physicians, nurses, pharmacists, and health education counselors. Their patient population represents over 200 AI tribes and over 30 AN villages. Although most patients live within 20 miles of HHC, some patients drive up to 70 miles for their medical services. HHC does not have mammography equipment. A third of their female patients are over age 40 and should, therefore, be having mammograms. A mobile unit from the Oklahoma office comes to HHC three days a year to serve these women.

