##### Sample Size Justification

Specific Aim 3 of this study is to assess the difference in satisfaction of mammogram experiences between American Indian women who had mammogram in facilities affiliated to the Indian Health Service (IHS) and American Indian women who had mammogram in facilities not affiliated to the HIS. The sample size is justified based on the global satisfaction score of the questionnaire developed in Specific Aim 2 for satisfaction regarding the mammogram experience. Assuming the total score follows normal distributions and a frequency distribution of 10% (women with mammograms from IHS facilities) and 90% (women with mammograms from non-IHS facilities) in these two groups, a total sample size of 300 American Indian women, expected to be 30 from IHS-affiliated and 270 from non-IHS-affiliated institutions, will provide 80% power at 0.05 significance level to detect an effect size of 0.54 in the total score of satisfaction according to a two-sided two-sample t-test.

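### The Aim 3 IHS versus non-IHS comparison is planned as raw averages of two self-selected groups, and the regression already planned for the same score is not tied to it

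*Protocol article*

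**What the plan says.** Study Aims and Hypotheses gives Aim 3 one hypothesis: satisfaction varies between women served inside and outside the IHS system. Mammography Satisfaction Variation sets the endpoint: "The primary outcome will be the global satisfaction score on the AIMS with secondary outcomes being the derived AIMS subscales". It then plans two things for that score.

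- A regression: "To model the global AIMS scores on individuals adjusting for individual factors (age, race/ethnicity, etc.), linear regression models will be developed". IHS status is not named as a term.
- In a separate paragraph, the IHS comparison: "This will be done by averaging the global AIMS scores for participants with an Indian Health Service-sponsored mammogram", and the same for women with a non-IHS mammogram.

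Sample Size Justification powers this contrast with 300 women, 30 IHS and 270 non-IHS. It states that this number "will provide 80% power at 0.05 significance level to detect an effect size of 0.54". The calculation is for a t-test comparing the two groups, with no adjustment.

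Under AIMS Recruitment, women come from one IHS clinic by staff referral and waiting-room posters, and from community events. The article says this mix gives better access to women who do not use IHS for mammograms. The survey's demographic list (Development of an American Indian Mammography Satisfaction (AIMS) Survey) covers age through date of birth, education, marital status, income, employment, race/ethnicity, number of past mammograms and breast malignancy history. Insurance is not on it.

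**The concern.** The comparison is not randomised, and the two recruitment routes are likely to deliver IHS and non-IHS users in different proportions. The Background names age, income, education, insurance and access as drivers of mammography use, and the focus groups are stratified by age and residence. If such factors also affect how women rate a service, the raw difference in means mixes who uses IHS mammography with how IHS mammography performs. The Discussion wants any difference to prompt further study and future interventions, so a wrong attribution would carry forward.

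This is a stated choice. The article gives the IHS contrast its own method, averaging, one paragraph after describing adjusted models of the same outcome. It is also the only hypothesis with a power statement.

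Facility is a second, weaker strand. The recruiting clinic has no mammography equipment: "A mobile unit from the Oklahoma office comes to HHC three days a year to serve these women". The Background reports of a six-facility comparison: "This study found considerable variation among facilities with respect to patient-reported pain". The Discussion expects similar variation here. If few units supply the IHS mammograms, the contrast partly compares units.

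**Working it through.** **1. The plan's own figure.** Inputs from Sample Size Justification: n = 30 and 270, effect 0.54 SD, two-sided 0.05.

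SE = √(1/30 + 1/270) = √0.03704 = 0.1925 SD.

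Power ≈ Φ(0.54/0.1925 − 1.96) = Φ(0.846) = 80.1%. The exact noncentral t (298 df) gives 79.9%, with a detectable effect of 0.541 SD. The stated figure reproduces.

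**2. Effect of patient mix on the raw test.** The documents give no size for this, so the inputs are assumed. A covariate that differs by 0.5 SD between groups and correlates 0.3 with satisfaction within groups shifts the raw difference by 0.5 × 0.3 = 0.15 SD. With no service difference:

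P(significant) ≈ Φ(b/SE − 1.96) + Φ(−b/SE − 1.96)

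| Shift b (SD) | P(significant) |
|---|---|
| 0 | 5% |
| 0.10 | 8% |
| 0.15 | 12% |
| 0.20 | 18% |
| 0.30 (two such covariates) | 34% |

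**3. Precision of the adjusted estimate.** Let R²x be the share of IHS status, and R²y the share of the score, explained by the covariates (assumed; five covariates).

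SE(adjusted) = 0.1925 × √[(1 − R²y)/(1 − R²x)]

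| R²x | R²y | Power at 0.54 SD | Detectable effect (SD) |
|---|---|---|---|
| 0.1 | 0 | 75.6% | 0.57 |
| 0.2 | 0 | 70.6% | 0.61 |
| 0.3 | 0 | 64.8% | 0.65 |
| 0.2 | 0.2 | 79.9% | 0.54 |
| 0 | 0.2 | 87.8% | 0.48 |

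Adjustment can cost precision, leave it alone or improve it.

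**4. Facility clustering, as a bound.** The intraclass correlation (ICC) and facility counts are assumed.

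Variance = (1/30)[1 + (m₁ − 1)ICC] + (1/270)[1 + (m₂ − 1)ICC], where m₁ and m₂ are women per IHS and non-IHS facility.

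False-positive rate of the naive test = 2[1 − Φ(1.96/√(variance/0.03704))].

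- One IHS unit, 20 others (m₁ = 30, m₂ = 13.5). ICC 0.02: variance 0.0573, ratio 1.55, rate 12%. ICC 0.05: variance 0.0877, ratio 2.37, rate 20%.
- Five IHS units, 27 others (m₁ = 6, m₂ = 10). ICC 0.02: rate 6.3%. ICC 0.05: rate 8.2%.

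**The case against.** The strongest reply is that Aim 3 is descriptive. The hypothesis speaks of variation, the analysis section opens as an exploratory account, and nowhere does the article claim a causal effect of IHS care. For a descriptive question the raw mean difference is a legitimate target, and a significant result caused by patient mix is a true difference between the groups. This stands in part: the 12% and 34% in step 2 are errors only if the result is read as a difference in IHS service. The risk is that the Discussion invites that reading by linking differences to future interventions.

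Next, the regression's covariate list is open-ended and might include IHS status. That is possible, but the IHS contrast gets a separate stated method, so the text at least permits the powered hypothesis to be tested unadjusted.

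Third, the evidence for confounding is indirect. The Background lists drivers of mammography use, whereas every respondent has already been screened. This is why the sizes in step 2 are illustrations.

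Three stronger readings are tempting, and the documents do not support them.

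- *All 30 IHS women share the mobile unit.* The article describes that unit at one clinic. Recruitment also covers events in four reservation cities, so other IHS facilities may contribute.
- *The t-test assumes equal variances.* Sample Size Justification says only "according to a two-sided two-sample t-test". It does not specify a pooled test, so no unequal-variance criticism follows.
- *The power calculation is wrong.* It reproduces for the test it names.

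The data gaps are also smaller than the demographic list suggests. Table 3 (pilot eligibility) requires a home address, and the survey section anticipates items on facility location and type.

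**Conclusion.** The point holds as a mismatch between the stated comparison and the regression already planned. The one powered contrast is left as raw averages in self-selected groups, so measured differences in patient mix that the study could adjust for may be taken for differences in IHS service. The size cannot be fixed from the documents: assumed shifts of 0.10-0.30 SD give 8-34% significant results with no service difference.

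The 80% power at 0.54 SD is valid for an unadjusted test on independent observations. For the adjusted contrast, the detectable effect would be 0.57-0.65 SD if covariates explain 10-30% of IHS status and none of the score, about unchanged if they explain both equally, and smaller if they mainly explain the score.

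The 12-20% clustering figures are a worst case, resting on one IHS unit and an ICC of 0.02-0.05. Regression removes measured mix only. It cannot cure self-selection into the survey, and if one or two units supply the IHS mammograms, no model separates the unit from the system.

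**What to change.** - **Main estimate.** Make the Aim 3 estimate the IHS coefficient in the planned linear model of the global score. Adjust for prespecified covariates already collected (age, education, income, employment, race/ethnicity) plus recruitment route, with heteroscedasticity-robust standard errors. Report the raw group means as descriptive.
- **Prior mammograms.** Use this count only in a sensitivity analysis. The Background says earlier experience affects repeat use, so the count may follow from satisfaction.
- **Survey fields.** Before the survey is locked, add the last mammography facility, and add insurance and residence if not otherwise obtained. Clustering cannot be examined later if facility was never recorded.
- **Clustering.** Use facility-clustered errors or a facility random intercept only if several IHS facilities contribute. Otherwise limit the conclusion to the units observed.
- **Power statement.** Say that 80% at 0.54 SD refers to the unadjusted, independent-observations test, and give a range for the adjusted model as in step 3.

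The cost is a few sentences of analysis text and up to three short survey fields. Recruitment route is probably the covariate most closely tied to IHS status, so it may cost the most precision; the range should allow for that.
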